### Inclusion criteria

Participant is willing and able to give informed consent for participation in the study.Male or female, aged 18 years or above.BMI of ≥30 kg/m^2^.Diagnosed with type 2 diabetes, (as defined by an HbA1c≥48 mmol/mol (6.5%) at time of diagnosis).Patients must have undergone diabetic retinopathy screening within the last 12 months.

### Exclusion criteria

History of, or features indicative of, an eating disorder.Pregnant, breast feeding, currently undergoing fertility treatment or planning to become pregnant during the course of the study.Recent myocardial infarction (MI) or cerebrovascular accident (CVA) (<3 months).Uncontrolled ischaemic heart disease, critical ischaemia, uncontrolled hypertension, uncontrolled cardiac arrhythmia, cardiac conduction abnormality (eg, long QT syndrome).Cardiac failure (grade II, III or IV New York Heart Association).Renal failure (chronic kidney disease (CKD) stage 4 or 5).Active treatment for cancer (other than skin cancer treated with curative intent by local treatment only).Intercurrent serious infection at time of recruitment.Diagnosed with a significant psychiatric disorder or substance abuse.Serious neurological disorder, including epilepsy.Recently undergone significant surgery (<6 months).History of bariatric surgery, including gastric banding.Are currently using a ‘fasting’/low-energy diet.Unwilling to consider any dietary changes.Unable to understand English.Are currently using insulin or sodium-glucose co-transporter 2 (SGLT2) inhibitor therapy.Non-proliferative retinopathy level R2 or more severe (ie, any level more severe than ‘background’ non-proliferative diabetic retinopathy, R1), proliferative diabetic retinopathy or maculopathy.HbA1c ≥93 mmol/mol (10.5%).Recruiting physician feels they are inappropriate for recruitment due to any other reason.

### Participant flow

Baseline appointments will be conducted with either the practice nurse or a member of the research team at participants’ own GP practice, during which informed consent will be sought, eligibility formally assessed and baseline measurements collected. The participants will then be randomised to one of the two trial arms. Participants allocated to the control arm will continue to an appointment with the practice nurse for ‘usual care’ dietary advice. Participants randomised to receive the intervention will proceed to an appointment with healthcare professionals (practice nurse and then GP) at their practice, during which the intervention materials and advice will be delivered, and medication regimens reviewed for those participants on antihypertensive, hypoglycaemic or lipid-modifying medications. Those in the intervention arm will subsequently be invited to attend for week 2, 4 and 8 study visits, at which further samples and measurements will be obtained. All participants will be invited for a final 12-week follow-up visit, at which time all outcome measures will be repeated. After completion of the 12-week follow-up period, participants will be invited to participate in qualitative focus groups to further explore their experience of this intervention. Participant flow through the study is outlined in figure 1.

**Figure 1 F1:**
[figure not shown]
Participant flow through the study. CRN, clinical research network DIAMOND, Dietary Approaches to the Management Of type 2 Diabetes.

### Sample size

The total number of participants recruited for this study will be 30. As this is a feasibility study, it has not been powered to detect a statistically significant difference in efficacy between the arms. In determining thresholds for progression criteria, based on previous trials of a similar nature, we expect at least 75% achievement.^27 28^ If so, the 95% CI will exclude 60%, and therefore we have set this as the progression criteria for each criterion, requiring a sample size of 30 participants allocated in a 2:1 ratio, intervention:control.

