**Methods and analysis:**

This is a feasibility randomised controlled trial (RCT) with embedded qualitative study. Thirty adult patients with type 2 diabetes and body mass index ≥30 kg/m^2^ in 2–4 general practices will be randomised 2:1 intervention or control and followed up over 12 weeks. The intervention diet comprises 8 weeks of a low-carbohydrate food-based diet providing around 800 kcal/day, followed by 4 weeks of weight maintenance. This programme will be delivered by practice nurses, who will also support patients through goal-setting, motivation and self-monitoring across four appointments, and provide a self-help booklet with recipes, shopping lists and other behavioural support. Primary outcome measures of feasibility will be met if CIs do not cross the following proportions: that 60% of intervention group participants attempt the dietary intervention, healthcare professionals conduct the intervention delivery session with at least 60% of essential elements present and 60% of participants attend the final follow-up session. Secondary outcome measures will assess process and qualitative measures, as well as exploratory outcomes including change in haemoglobin A1c and change in weight.

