### Outcomes

#### Primary

The primary objective of this study is to test the feasibility of a low-carbohydrate, low-energy, behavioural intervention, comprising targeted advice from a health professional combined with written dietary information, to promote weight loss and improved glycaemic control in patients with type 2 diabetes. This feasibility study will then determine whether to progress to a full randomised control trial.

The following progression criteria will determine whether to progress to a full trial:That 60% of allocated ‘intervention’ group participants attempt the dietary intervention after randomisation.(Evaluated by documentation after intervention visit; assessed as the proportion of patients who agree to start the dietary intervention, as recorded by the nurse delivering the intervention session.)Fidelity of intervention delivery: That healthcare professionals conduct the intervention delivery session with at least 60% of essential elements present.(Evaluated by assessment of audio recorded consultations against a checklist of pre-specified essential elements.)That 60% of participants attend the final follow-up session.(Documentation of final study visit.)

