### Statistical analysis

Primary outcome measures for this study are progression criteria, to inform any future RCT powered to detect an intervention effect. Analysis for progression criteria will use data from all participants recruited to the trial. Descriptive statistical methods along with inferential statistics presenting CIs will be used to analyse and report progression criteria.

Secondary outcome measures for this study include process measures and exploratory effectiveness measures. Both measures will use all collected data, including that from participants who have not completed the trial, and from participating practices (where pertaining to proportions of patients identified as eligible, and responding to invitations to participate). Descriptive comparative summary statics (eg, difference in means or proportions, together with 95% CIs, comparison with baseline and overall change compared with control group) will be used.

Acceptability and experience of the intervention by participants and healthcare professionals will be collected as qualitative data from interviews and focus groups conducted after intervention completion. These data will be qualitatively analysed using thematic analysis, and reported descriptively.

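### At 75% achievement the 95% CI does not exclude 60% for the attempt criterion (about 20 participants), and for attendance (30) it is borderline, so the sample-size statement is wrong as written

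*Protocol article*

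**What the plan says.** The protocol article's Sample size section fixes the total: "The total number of participants recruited for this study will be 30". The planning rate follows: "based on previous trials of a similar nature, we expect at least 75% achievement". The precision claim is: "If so, the 95% CI will exclude 60%, and therefore we have set this as the progression criteria for each criterion", and the size is derived from it, "requiring a sample size of 30 participants allocated in a 2:1 ratio, intervention:control".

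The abstract turns this into a decision rule: "Primary outcome measures of feasibility will be met if CIs do not cross the following proportions", with 60% as the proportion for each criterion. The Primary outcomes section lists the same criteria as plain 60% levels, with no interval. Its first criterion is limited to the intervention arm: "That 60% of allocated ‘intervention’ group participants attempt the dietary intervention after randomisation". Attendance at the last visit is counted over all participants. Fidelity is scored from audio recordings against a checklist of essential elements, and no number of recordings is given.

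**The concern.** The sentence on the CI is the only quantitative reason given for 30 participants, and it is said to hold for every criterion. Yet 2:1 allocation of 30 leaves about 20 in the intervention arm, and the attempt criterion is a proportion of those 20. An interval based on 20 is clearly wider than one based on 30.

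If the sentence is wrong, the go/no-go rule asks for more than its authors appear to think. A programme performing at the low end of the planning range could then be declared not feasible. There is also a risk to the decision itself. A result such as 15/20 meets the plain 60% wording in the outcomes section but not the CI rule in the abstract, so the choice between them could be made after the data are seen.

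**Working it through.** **Inputs.** Total 30, ratio 2:1, planning rate 75%, threshold 60% and 95% confidence (Sample size). CI rule (abstract). Denominators (Primary outcomes): attempt 30 × 2/3 = 20, attendance 30. Sidedness and interval method are not stated, so two-sided limits are taken as standard and one-sided limits tried as a variant.

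**Step 1: the plan's own claim, on all 30.** Wald limits are p ± 1.96 × √(p(1−p)/n).
- 0.75 ± 1.96 × √(0.1875/30) = 0.75 ± 0.155, or 59.5% to 90.5%. This just includes 60%.
- Wald n for a lower limit of 60% at 75%: 0.1875 × (1.96/0.15)² = 32.01, so 33.
- Exactly 75% of 30 is 22.5, which cannot occur. The lower limit at 22/30 is 57.5% (Wald), 55.6% (Wilson) or 54.1% (exact). At 23/30 it is 61.5% (Wald), 59.1% (Wilson) or 57.7% (exact).

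The claim is therefore not quite reproduced at 30, and which side of 60% the limit falls on depends on the method.

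**Step 2: the attempt criterion, 15/20.**
- Wald: 0.75 ± 1.96 × √(0.1875/20) = 0.75 ± 0.190, or 56.0% to 94.0%.
- Wilson: (0.75 + 0.0960 ± 1.96 × √(0.009375 + 0.002401)) / 1.1921, or 53.1% to 88.8%.
- Exact (Clopper-Pearson): 50.9% to 91.3%.
- One-sided 95% lower bounds: 59.1% (Wald), 56.8% (Wilson), 54.4% (exact).

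Every version includes 60%.

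**Step 3: smallest counts that exclude 60%, two-sided.**
- n = 20: 16/20 by Wald (0.80 − 1.96 × √(0.16/20) = 62.5%); 17/20 by Wilson or exact (exact lower limit 56.3% at 16/20 and 62.1% at 17/20).
- n = 30: 23/30 by Wald; 24/30 by Wilson or exact (exact lower limit 61.4% at 24/30).

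**Step 4: chance of reaching those counts.** Binomial upper tail P(X ≥ c | n, true rate):

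| True rate | Attempt, 17/20 (Wilson/exact) | Attempt, 16/20 (Wald) | Attendance, 24/30 (Wilson/exact) | Attendance, 23/30 (Wald) |
|---|---|---|---|---|
| 75% | 22.5% | 41.5% | 34.8% | 51.4% |
| 80% | 41.1% | 63.0% | 60.7% | 76.1% |
| 85% | 64.8% | 83.0% | 84.7% | 93.0% |
| 90% | 86.7% | 95.7% | 97.4% | 99.2% |

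**Step 5: the plain 60% wording.** Read as a point estimate, 60% is 12/20 or 18/30. At a true 75% these are reached with probability 95.9% and 97.8%. At 15/20 the point-estimate reading says progress and the CI rule says do not.

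**The case against.** Several points on the other side stand.

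- **The result at 30 is a near miss.** The Wald limit of 59.5% rounds to 60%, 23/30 clears 60% by Wald, and a one-sided 95% Wald bound at 75% is 62.0%. A reader might infer that the statement is plainly false at 30; the text, which names neither method nor sidedness, does not support that.
- **75% is the low end of the expectation, not its centre.** A reader might infer that a programme performing as expected would usually fail. That holds for the attempt criterion at 75% but not across the range: at a true 85% or 90% it passes more often than not by any of these intervals.
- **Fidelity cannot be put on a denominator of 20.** It is a share of checklist elements, and the number of scored sessions is not given. Treating it as 20 yes/no results and multiplying three pass probabilities would need that assumption as well as independence, and the documents give neither.
- **The observed rate need not fall short half the time.** At a true 75%, it falls below 75% in 38% of trials at n = 20 and 49% at n = 30.
- **The Statistical analysis section conceals nothing.** "Analysis for progression criteria will use data from all participants recruited to the trial" describes the analysis set, and the outcomes section already limits the attempt criterion to the intervention arm. Naming the interval method can be left to a statistical analysis plan.

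It may also be said that a feasibility trial needs no power. The article's disclaimer, however, concerns efficacy between arms. For progression it chose a CI rule and derived its size from it. None of these points rescues the attempt criterion at 15/20.

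**Conclusion.** The sample-size sentence is wrong as written. It claims exclusion of 60% for each criterion, and for attempting the diet this fails at 75% under all three intervals above, two-sided or one-sided. For attendance it is borderline and depends on the method. No conclusion is drawn for fidelity.

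At a true rate of exactly 75% the attempt criterion is more likely to fail than pass, even by the most lenient interval (41.5%). Attendance ranges from about one in three to an even chance. The shortfall shrinks quickly as the true rate rises and is small at 90%.

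The pass probabilities assume 20 and 30 participants, independent participants with a common true rate, and the abstract's CI rule as the operative one. The abstract and the Sample size section favour that rule; the outcomes section does not state it.

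**What to change.** Keep 30 participants. In the Sample size section, replace the precision sentence with what the design delivers: with about 20 intervention participants, 15/20 gives an exact 95% CI of 51–91%; by Wilson or exact interval, excluding 60% requires at least 17/20 attempting the diet and at least 24/30 attending the final visit.

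If those cut-offs are stricter than intended, restate the progression rule before data are seen. In either case, make the plain 60% wording in the Primary outcomes section and the CI rule in the abstract agree.

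The cost is protocol wording and the usual amendment. No extra participants are needed. The drawback is that the stated precision will look less favourable than it does now.

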### Randomisation

All eligible, consenting participants will be randomised to one of the two trial arms (intervention or control), using permuted block design randomisation with blocks of 3 and 6. Allocation will be stratified by practice. An independent researcher will generate the set of sequences and assign participants to the intervention groups using sequentially numbered sealed envelopes to ensure allocation concealment until interventions are assigned. Due to the nature of this study, it will not be possible to further blind participants, clinicians or some of the study team to the treatment allocation beyond this point.

### Intervention

#### The DIAMOND programme

The active intervention is a behaviourally informed, low-carbohydrate, low-energy diet delivered by healthcare professionals at a GP practice. It draws on the motivational value of the relationship between the healthcare professional and the patient, but provides almost all the technical knowledge-transfer through the use of structured materials such as meal plans, thus addressing the uncertainties and lack of confidence expressed by health professionals about giving dietary advice.^29^ The intervention aims to improve patients’ adherence to the programme by providing a structured simple behavioural support programme, including goal-setting, planning, feedback and problem-solving. It is designed to induce rapid changes in dietary composition and weight loss, followed by a sustainable maintenance programme. The intervention is envisaged to take 10–15 min of support from the GP and 80 min from the nurse to deliver over four sessions of support (baseline, week 2, week 4 and week 8).

This intervention was designed following the principles of the person-based approach.^30^ It involved examining recent systematic reviews, reviewing qualitative studies and process assessments of these types of interventions and developing the behavioural and dietary intervention programme with a multi-disciplinary team comprising a diabetes-specialist dietitian and clinician, primary care physicians and patient involvement. Two groups of patients with type 2 diabetes, including those who had recently tried variations of a low-carbohydrate, low-energy diet, also met to discuss the intervention and to inform and advise on the dietary and behavioural support components.

The dietary component of this intervention consists of a low-carbohydrate and energy restricted diet (800–1000 kcal/day) for 8 weeks, transitioning to a 4-week maintenance period. The core principles include: advice to exclude sugary and starchy foods high in carbohydrates (eg, biscuits, confectionery, bread, pasta, potatoes) entirely from their diet (with the exception of dairy and limited fruit intake), strict portion control and avoiding energy-dense foods. Standardised ‘healthy eating’ advice regarding fresh vegetables, and lean meat and fish, is also included. After the initial 8-week intensive weight loss phase, participants will be advised to gradually increase their energy intake, reintroducing one ‘normal-sized’ meal at a time, until they remain weight stable, but with guidance on maintaining a sustainable lower-carbohydrate diet in the longer term.

The design of this intervention has been additionally informed by behavioural analysis, identifying domains of the Behaviour Change Wheel^31^ and Theoretical Domains Framework^32^ to promote successful behaviour change. Using these frameworks, the key influencing factors which have been targeted are: psychological capability (including knowledge, skills, decision processes and behavioural regulation), social and physical opportunity (social influences and environmental context), reflective motivation (beliefs about capabilities and consequences, optimism, intentions, goals and reinforcement).

To address these components, the intervention will include:A brief behavioural intervention consisting of both dietary and motivational advice, including the rationale behind the intervention, to be delivered by a healthcare professional in primary care. The dietary advice includes the essential features of the diet—low energy and low carbohydrate content, as described above.Written resources, including advice for meal planning and food selection, and suggested recipes for ‘real food’ choices—to empower patients with the knowledge and skills for decision-making about food.Personalised realistic goal setting (eg, change in weight, HbA1c, number of diabetic medications).Diary to record self-assessment of programme adherence.Structured healthcare professional follow-up, to provide support and contingency planning, and feedback on progress. Additionally, patients will be able to self-monitor their health with the use of home fingerprick-testing blood glucose meters, and blood pressure (BP) machines, for additional motivation and monitoring of progress.Feedback from healthcare professional on personal changes in health parameters as a consequence of the intervention (changes in weight, BP, HbA1c).

#### Comparator

Participants randomised to the control arm will receive usual care at their week 0 study visit, comprising a single face-to-face appointment with a healthcare professional, during which they will receive standard dietary and lifestyle information based on the Diabetes UK ‘what is a healthy balanced diet for diabetes’ leaflet. If their managing GP or nurse feels they warrant referral for further diabetic care or input (eg, diabetes education course), or intensification of medications, and would ordinarily have pursued this as part of their routine care outside of the trial, this will be permitted as forming part of ‘usual care’, but will be documented.

### Outcomes

#### Primary

The primary objective of this study is to test the feasibility of a low-carbohydrate, low-energy, behavioural intervention, comprising targeted advice from a health professional combined with written dietary information, to promote weight loss and improved glycaemic control in patients with type 2 diabetes. This feasibility study will then determine whether to progress to a full randomised control trial.

The following progression criteria will determine whether to progress to a full trial:That 60% of allocated ‘intervention’ group participants attempt the dietary intervention after randomisation.(Evaluated by documentation after intervention visit; assessed as the proportion of patients who agree to start the dietary intervention, as recorded by the nurse delivering the intervention session.)Fidelity of intervention delivery: That healthcare professionals conduct the intervention delivery session with at least 60% of essential elements present.(Evaluated by assessment of audio recorded consultations against a checklist of pre-specified essential elements.)That 60% of participants attend the final follow-up session.(Documentation of final study visit.)

#### Secondary

A mixture of quantitative and qualitative methods will be used to assess process measures and effectiveness measures. This feasibility study is not powered to detect statistical differences in efficacy outcomes but will examine the following parameters in order to test trial procedures, process, resources and management, to aid sample size estimates for a future trial, to determine the most appropriate primary outcome measures for a future trial and to inform further development of the intervention strategy.

#### Process measures

Percentage of eligible patients, as a proportion of the total population of patients in a practice, with type 2 diabetes.Percentage of people who fulfil the recruitment criteria who accept the invitation to participateProportion of patients who enrol in the study who are deemed to have with ‘suboptimal control’ (HbA1c above the National Institute for Health and Care Excellence target of ≥7%).Participant adherence to the protocol: including, change in dietary composition (low-carbohydrate, energy restricted—assessed using 24 hours dietary recall questionnaires); participants’ self-reported concordance with the intervention; availability of data for outcome measures; attendance at follow-up sessions; contamination of the control group (ie, those who choose to follow the principles of the intervention (ie, follow a low-carbohydrate diet), despite being allocated to the control group). This will be assessed using 24 hours dietary recall questionnaires to establish change in dietary composition (frequency of carbohydrate consumption, energy restriction) of control group participants.Difference between ‘baseline’ HbA1c value and that used from the latest record as inclusion criteria.Serious adverse events (SAEs) reported up to the end of the 12-week study participation period.

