### Questionnaires

During study follow-up visits, patients will be asked to complete questionnaires to assess the following measures:*Quality of life:* the PAID score, a 20-item questionnaire measuring problems related to emotions, treatment, food and social support,^33^ will be measured at baseline and 12 weeks.*Dietary composition:* a 24-hour dietary recall questionnaire will be used to assess intake of different food groups at baseline, 2, 8 and 12 weeks.*Motivation:* self-reported motivation and perceptions across domains of diet, health and diabetes control will be assessed using a 6-point questionnaire at baseline and 12 weeks.*Self-reported adherence to intervention:* self-reported adherence to the three core components of the dietary intervention will be assessed at 2, 4, 8 and 12 weeks.

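### On the text shown, controls give only one dietary recall after randomisation, at week 12, so dieting that a control started and stopped earlier would tend to go uncounted as contamination

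*Protocol article*

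**What the plan says.** All references are to the protocol article.

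- **Process measures** lists, under adherence to the protocol, "contamination of the control group (ie, those who choose to follow the principles of the intervention", and explains this as following a low-carbohydrate diet despite allocation to control. No time window is given. On method it says: "This will be assessed using 24 hours dietary recall questionnaires to establish change in dietary composition". No other instrument is named for contamination.
- **Questionnaires** sets the place and timing: "During study follow-up visits, patients will be asked to complete questionnaires to assess the following measures", and "a 24-hour dietary recall questionnaire will be used to assess intake of different food groups at baseline, 2, 8 and 12 weeks". No arm is stated.
- **Participant flow** gives the visits by arm: "Those in the intervention arm will subsequently be invited to attend for week 2, 4 and 8 study visits". For the end of the study: "All participants will be invited for a final 12-week follow-up visit".
- **Comparator** says that controls "will receive usual care at their week 0 study visit, comprising a single face-to-face appointment with a healthcare professional".
- **The DIAMOND programme** describes the restricted diet as lasting "for 8 weeks, transitioning to a 4-week maintenance period".
- **Sample size** gives 30 participants, allocated 2:1.

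**The concern.** Taken one at a time, these sections look complete. Read together, they leave controls with no study visit between week 0 and week 12, and so no occasion on which to complete the week-2 and week-8 recalls.

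The behaviour that could be missed is plausible. The Introduction says that few people keep to a low-energy diet indefinitely, and it offers declining adherence as one reason why the benefit of low-carbohydrate diets fades. Patient involvement reports that the study grew out of local patient demand to know more about such diets. Allocation is open, individuals are randomised within practices, and practice nurses see patients in both arms. A control might therefore try the diet for some weeks and give it up. Such a person fits the protocol's definition of contamination but would not be picked up by its named measure.

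At stake is how well a secondary process measure does its job. The Secondary outcomes section says these measures are there to test trial procedures and to help plan a future trial. Contamination also bears on how the exploratory differences between arms are read. If the data are not collected, no later analysis plan can recover them.

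**Working it through.** The protocol states no figure to reproduce here. The check is a cross-tabulation of the recall time points (Questionnaires) against the visits by arm (Participant flow, Comparator).

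| Time point | Recall listed | Intervention visit | Control visit | Recall obtainable, intervention | Recall obtainable, control |
|---|---|---|---|---|---|
| Baseline | yes | yes | yes | yes | yes |
| Week 2 | yes | yes | no | yes | no |
| Week 4 | no | yes | no | – | – |
| Week 8 | yes | yes | no | yes | no |
| Week 12 | yes | yes | yes | yes | yes |

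**Counts per participant**

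- Baseline measurements are taken before randomisation, so the baseline recall cannot show contamination.
- Recalls after baseline: intervention 3 (weeks 2, 8, 12); control 1 (week 12).
- Recalls within the 8-week intensive phase: intervention 2 (weeks 2, 8); control 0.
- The one control recall comes 12 − 8 = 4 weeks after that phase ends.
- Number of controls: 30 × 1/3 = 10.

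**Other sources in the article.** Patient focus groups draw on the intervention group only (Qualitative substudy). The self-report questionnaire at weeks 2, 4, 8 and 12 concerns adherence to the intervention. Weight and HbA1c at week 12 might hint at dieting but are not named as contamination measures. No telephone, postal or online recall for controls is described.

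**Illustration of the under-count (assumed numbers).** Suppose k controls diet during weeks 0 to 8, each is still dieting at week 12 with probability s independently of the others, and the recall identifies everyone who is. The chance that week 12 shows none of them is

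P = (1 − s)^k.

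For k = 3 of 10:

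- s = 0: 1³ = 100%
- s = 0.25: 0.75³ = 42%
- s = 0.50: 0.50³ = 12.5%
- s = 1: 0³ = 0%

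The range runs from certain to miss to certain to see. The protocol gives no value for k or s.

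**Precision with 10 controls.** For an observed 0 of 10, the exact 95% upper limit is 1 − 0.025^(1/10) = 30.8%. The measure is imprecise on any schedule.

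**The case against.** **The gap is inferred, not stated.** Questionnaires does not restrict the recall by arm, and Figure 2, where a schedule by arm would be expected, is not shown. Fasting blood sample likewise lists an 8-week sample without naming an arm, so these sections may simply list time points. This stands, and it limits confidence. If Figure 2 does give controls recalls at weeks 2 and 8, the text on who attends which visit would still need to be squared with it.

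**A reader might infer that dieting by controls in the first 8 weeks is invisible altogether.** The documents do not support that. A control who starts early and is still dieting at week 12 can be detected then. Week 12 also remains a relevant point for a low-carbohydrate contrast, because the intervention arm is guided to keep to a lower-carbohydrate diet after week 8.

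**A reader might infer that the measure as a whole is biased towards finding no contamination.** That is not established. Missed early dieting pushes the count down, but a single-day recall can also misclassify a control who had an atypical low-carbohydrate day. The net effect has not been sized.

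**A reader might infer that contamination decides whether the full trial can randomise individuals within practices.** No section says so. It is not one of the three progression criteria, and the unit of randomisation is not among the uses listed for secondary measures. Nor is a between-arm diet contrast in the intensive phase a named outcome.

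**A reader might gauge the defect by the share of days covered:** 1 of 84 for controls. That figure mostly describes 24-hour recall as an instrument. With all three recalls after baseline it would be only 3/84 = 3.6%, the same as in the intervention arm.

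**Conclusion.** The point holds in limited form. On the text shown, the only named contamination measure is collected once after randomisation in controls, at week 12, and not at all in the intensive phase. Low-carbohydrate or low-energy dieting that a control stopped before week 12 is not directly observed and would tend to be under-counted; dieting that continues to week 12 is not lost.

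The size is 1 recall against 3 after baseline, and 0 against 2 in the intensive phase, for about 10 controls. How much contamination would be missed depends on how many controls diet early and how many have stopped by week 12. The protocol gives neither, so the illustration shows only a range.

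The conclusion assumes that recalls are taken only at study visits and that Figure 2 adds no control-arm contact. It touches a secondary process measure that informs the design of the full trial. The three progression criteria are unaffected.

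**What to change.** 1. At the existing week-12 visit, ask every control whether they have followed a low-carbohydrate or low-energy diet at any time since randomisation, for how long, and whether they saw the trial materials.
2. In Process measures, define contamination from these answers together with the week-12 recall.
3. In Questionnaires, state which recall time points apply to which arm, in agreement with Participant flow and Figure 2.

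The cost is a few extra questions for about 10 people at a visit they already attend, and a sentence or two of text. The downside is the error of retrospective self-report over 12 weeks.

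Collecting the week-2 and week-8 recalls from controls remotely (10 × 2 = 20 recalls) is optional and not required. It would put observations inside the intensive phase, but it adds contact to an arm meant to have a single usual-care appointment, and that contact could itself prompt dieting. The article describes telephone, text and email contact for recruitment only, so remote collection would be a new procedure.
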